## **LIST OF ABBREVIATIONS**

|         |                                 |
|---------|---------------------------------|
| AFib    | Atrial Fibrillation             |
| FDA     | Food and Drug Administration    |
| INR     | International Normalized Ratio  |
| PI      | Principal Investigator          |
| PT      | Prothrombin Time                |
| TTR     | Time in Therapeutic Range       |
| UNIFESP | Federal University of São Paulo |
| UTN     | Universal Trial Number          |

## **1. Background**

### **1.1 Generic drugs**

In this introduction, we started describing that generic drugs represent a significant share of the drug market in Brazil and are completely incorporated in the country's health policies (1-4). We mentioned, however, that when it comes to the group of narrow therapeutic index drugs, which includes warfarin, even healthcare providers are suspicious of the equivalency of generic drugs to their branded counterparts (5-7,17-18). Next, we explained the technical requirement that generic drugs must fulfill in order to be considered equivalent to the brand medication, mentioning that some countries, but not Brazil, apply additional requirements to narrow therapeutic index drugs (7-12). Afterwards, we presented some studies that compared the effects of generic and branded warfarins. Randomized clinical trials did not show clinically meaningful differences between generic and branded warfarins, whereas observational studies brought more conflicting results. Nevertheless, none of these studies have used the generic and branded warfarins available in Brazil, limiting their applicability in our country (6, 13-16,19-21). Subsequently, we mentioned an issue that might arise when there is more than one generic drug available for a given brand medication: generics are devised to be equivalent to the brand medication, but not necessarily equivalent to each other (22). Finally, we presented the objectives of this project: run a randomized crossover clinical trial to assess whether the substitution of 1) branded warfarin by any of the generic formulations available in Brazil, or 2) substitution within the generic warfarins, is effective and safe for the patient with atrial fibrillation (AFib). We also added that patients with AFib diagnosis were selected because this was the most common diagnosis among the patients of anticoagulation clinics (23).

### **1.2 Atrial fibrillation**

In this section, we defined AFib and presented its prevalence, the characteristics of these patients and the consequences the disease may incur (24-29). We then presented the role that oral anticoagulation has in the treatment of patients with AFib and presented the drugs available for that treatment (30, 31). We then conclude that despite the benefits of the direct oral anticoagulants (32), warfarin is still the cheapest oral anticoagulant and will probably continue in use for many years.

### **1.3 Warfarin**

In this section, we described warfarin's characteristics: its mechanism of action, pharmacokinetics, the danger of use during pregnancy, side effects, mechanism of drug interactions, how to titrate the optimal dose and the importance of good management of the optimal dose (27, 32-35).

## **2. Objectives**

### **2.1 Overall objective**

Determine, through the mean international normalized ratio (INR) of patients, whether there is therapeutic equivalence between brand and generic warfarin sodium tablets in patients with atrial fibrillation in Brazil.

### **2.2 Specific objectives**

Assess the effects of the different warfarin tablets on:

- the mean INR of patients;
- the mean prothrombin time (PT);
- the proportion of thromboembolic events;
- the proportion of bleedings;
- the time in therapeutic range (TTR);
- adherence to treatment.

### 3. Hypothesis

The comparison of the mean INR between branded and generic warfarins is within the limit of 0.49 (two-sided, with a significance level of 5%) demonstrating therapeutic equivalence between them.

## 4. Methods

#### 4.1 Type of study

Randomized crossover controlled trial containing six treatment sequences and divided into four phases with different durations (Figure 1). The study is registered in [www.clinicaltrials.gov](http://www.clinicaltrials.gov) under the identification NCT02017197 and also has the Universal Trial Number (UTN) U1111-1155-4833.

[figure not shown]

## 4.2 Setting

Outpatient clinic of the Discipline of Cardiology, Department of Medicine, at the Federal University of São Paulo.

### 4.3 Participants

#### 4.3.1 Inclusion criteria

Patients who, according to a structured interview, or by review of their medical records, simultaneously meet all the following criteria will be included in the study:

- have a diagnosis of nonvalvular atrial fibrillation (documented by electrocardiogram and echocardiogram) (26);
- have a CHA2DS2VASc score greater than or equal to one (for whom is recommended anticoagulation with warfarin);
- are using warfarin;

- are over 18 years of age;
- and agree to participate in the study by signing the Informed Consent Form (Annex I)

#### **4.3.2 Exclusion criteria**

Patients who meet any of the following criteria will not be accepted:

- patients to whom the use of anticoagulants is contraindicated (patients using other anticoagulants, or with active bleeding, or with hypersensitivity to warfarin, or with ulcers);
- women of childbearing age, or who are pregnant or breastfeeding;
- patients with thrombocytopenia;
- patients with liver or kidney failure;
- patients with a history of bleeding episodes due to congenital deficiency of coagulation factors;
- patients enrolled in other clinical trials;
- patients not reaching a TTR of at least 70% in the first phase of the study (will be considered non-adherent to therapy);
- patients starting treatment with drugs that are contraindicated or that incur in moderate or major interactions when used concomitantly with warfarin, according to the online database Micromedex 2.0 (37) (Annex II).

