#### **4.4 Procedures**

Patients will be randomly allocated to one of the treatment sequences (A, B, C, D, E or F, Figure 1) and will start treatment with either the branded warfarin sodium or with one of the two generic versions available in the Brazilian market in August 2013. The first phase of the study will last 21 days. During this period, the patient, who had already been using warfarin, will start the randomly allocated treatment that will also be used in the second phase of the clinical trial. The use of the same treatment in phases one and two aims to avoid the carry-over effect without the interruption of anticoagulation treatment, which would be ethically unacceptable. The duration of three weeks for this phase is equivalent to about seven warfarin half-lives (38), the washout time for elimination of this drug. The duration of this phase will allow us to ensure that the formulation of warfarin used previously does not interfere with the results of the trial.

The second, third and fourth phases of the study will last 28 days each, in order to allow more weekly measurements to assess the effect of therapy with each of the formulations. In the second phase the patients will continue with the treatment started in phase one, and in the third and fourth phases will occur the change of warfarins according to the predetermined sequences for each group.

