#### **4.6 Statistical Method**

##### **4.6.1 Sample size**

At least 48 patients (8 in each group) will be needed in order to identify a clinically significant difference of 0.49 in the INR, considering a mean INR of 2.45 with standard deviation of 0.29, data reported for a branded warfarin in a published study (13). The sample was calculated based on the mean INR outcome, using the statistical method for quantitative outcomes (41) assuming  $\alpha = 5\%$  and  $\beta = 10\%$ , which result in a power of 90%. We plan to recruit 60 individuals (10 in each group) to compensate for possible dropouts or exclusions of patients.

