##### **4.6.2 Statistical analysis**

All statistical analyzes will have a significance level of 5%. Paired-samples t-tests (also called dependent T-tests) will be used for the outcome of mean INR and PT. Analysis will be performed by protocol for these outcomes i.e., data from patients who start treatment with any drugs that interact with warfarin as previously defined (list in Annex II) will be excluded from the final analysis.

The dichotomous outcomes (TTR, thromboembolic events, bleeding) will be analyzed by McNemar's test. Exploratory analyzes for patient subgroups are not planned. The dichotomous variables will be analyzed by intention to treat, considering the missing data as an unfavorable outcome, in which case a sensitivity analysis will be carried out to assess the robustness of the result.

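### The phase 1 TTR exclusion (and the interacting-drug exclusion when the drug is started during the trial) acts after randomisation and is not reconciled with the intention-to-treat analysis of TTR, bleeding and thromboembolism

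*Protocol*

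**What the plan says.** Protocol 4.3.2 (Exclusion criteria) begins "Patients who meet any of the following criteria will not be accepted". Two of its entries matter here:

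- on INR control, "patients not reaching a TTR of at least 70% in the first phase of the study (will be considered non-adherent to therapy";
- on concomitant drugs, with no time point given, "patients starting treatment with drugs that are contraindicated or that incur in moderate or major interactions when used concomitantly with warfarin".

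Section 4.4 (Procedures) places randomisation before phase 1. In that phase the patient "will start the randomly allocated treatment that will also be used in the second phase of the clinical trial". On duration it says "The first phase of the study will last 21 days" and "The second, third and fourth phases of the study will last 28 days each".

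Section 4.5 schedules INR, PT and clinical events twice a month, with no exception for any group of patients.

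Section 4.6.1 recruits 60 patients against a minimum of 48, "to compensate for possible dropouts or exclusions of patients".

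Section 4.6.2 makes mean INR and PT a per-protocol analysis that drops data from patients who start an Annex II drug. For TTR, thromboembolic events and bleeding, tested by McNemar's test, it says "The dichotomous variables will be analyzed by intention to treat, considering the missing data as an unfavorable outcome", with a sensitivity analysis. It does not mention patients below the TTR threshold.

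**The concern.** A patient rejected for poor INR control at day 21 has been randomised and has taken a study product for three weeks. Intention to treat requires that patient in the analysis, but the exclusion list says the patient is not accepted. No section says whether such a patient stays under event assessment, leaves the trial, or counts as missing.

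The TTR rule selects on a variable that the allocated product can affect and that 4.5.2 lists as an outcome. Section 4.3.2 treats a low TTR as non-adherence, although 4.5.2 measures adherence separately, by returned tablets. If one product controlled INR less well, patients starting on it would be excluded more often.

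The aim in section 1.1 is to learn whether substitution is effective and safe. If excluded patients are not followed, the event comparison rests on imputed events or on a selected group. This is not a detail to leave to a statistical analysis plan: such a plan can define analysis sets, but it cannot recover events that were never collected.

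**Working it through.** **1. Timing.** Allocation precedes phase 1 (4.4), and TTR is measured in phase 1 (4.3.2). The TTR criterion therefore cannot be checked before randomisation. The interacting-drug criterion could be checked at screening, but 4.6.2 applies the same Annex II definition to patients who start such a drug and removes their INR and PT data, so it also operates during the trial.

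**2. The plan's own figures.** Inputs from 4.6.1 are difference 0.49, SD 0.29, alpha 5% and power 90%; section 3 gives two-sided.

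- n per group = 2 × 0.29² × (1.960 + 1.282)² / 0.49² = 7.36, rounded up to 8.
- 8 × 6 sequences = 48, as stated.
- 60 − 48 = 12, an allowance of 12/60 = 20%.

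The sample size reproduces and is not in dispute. Nor is power the issue. With an assumed SD of differences of 0.29 × √2 = 0.41, the planned paired test would keep more than 99% power to detect 0.49 with only 24 patients.

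**3. Where each group is placed.**

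| Patient | 4.3.2 | INR and PT (4.6.2) | TTR and events (4.6.2) | Follow-up after the criterion is met |
|---|---|---|---|---|
| Phase 1 TTR below 70% | not accepted | not mentioned | intention to treat, not mentioned by name | not stated |
| Starts an interacting drug during the trial | not accepted | data removed | intention to treat | not stated |

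**4. If excluded patients leave and are imputed.** The protocol gives neither exclusion rates nor event rates, so both are assumed here. With true event proportion e and excluded fraction d, the apparent proportion is d + (1 − d) × e.

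| d | e = 2% | e = 5% |
|---|---|---|
| 10% | 0.10 + 0.90 × 0.02 = 11.8% | 0.10 + 0.90 × 0.05 = 14.5% |
| 20% | 0.20 + 0.80 × 0.02 = 21.6% | 0.20 + 0.80 × 0.05 = 24.0% |
| 40% | 0.40 + 0.60 × 0.02 = 41.2% | 0.40 + 0.60 × 0.05 = 43.0% |

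In counts, for 60 patients at e = 2% and d = 20%, there are 12 imputed events and 48 × 0.02 = 0.96 expected real ones.

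**5. Effect on McNemar's test.** The test uses only patients whose result differs between two products.

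- *Excluded at day 21:* missing in phases 2, 3 and 4, so unfavourable on all three products. Every pair is concordant and the test statistic does not change, though the reported proportions do.
- *Excluded during phase 3, no event in phase 2:* phase 2 is favourable and phase 4 is imputed unfavourable. That is a discordant pair with no event behind it. If the incomplete phase 3 also counts as missing, there is a second.

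**6. If excluded patients are left out.** No event is invented, but the analysis is no longer intention to treat.

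**The case against.** **The drug criterion need not conflict with 4.6.2.** It has no time point, and for drugs started later 4.6.2 confines the stated removal to INR and PT. This stands. It is tempting to say that both criteria can only be met after randomisation and that both contradict intention to treat. On timing, the text is certain for TTR only, and the conflict is clearest there.

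**The protocol does not order withdrawal.** A reader might infer from the opening of 4.3.2 and from the exclusions allowed for in 4.6.1 that these patients are removed and event follow-up ends. No section says so, and 4.5 schedules event assessment without exception. This stands: the defect is that the sections do not settle the matter, and the consequences in steps 4 to 6 are conditional.

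**The imputation rule and sensitivity analysis keep everyone in the denominator.** Formally true. But the rule then serves as the routine handling of patients whom the protocol itself excludes, and imputed events could far outnumber real ones.

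**The scale is unknown.** A reader might treat the full 12-patient allowance as day-21 exclusions and conclude that 12 × 3 = 36 of 60 × 3 = 180 patient-phases (20%) would be lost and the product comparison distorted to that extent. The documents do not support this. The allowance also covers dropouts, no exclusion rate is given, and day-21 exclusions add no discordant pairs.

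**The outcomes are secondary.** Mean INR is primary, and the trial was not sized for events. This limits the weight of the point but does not remove it.

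**Conclusion.** The point holds in a limited form. The phase 1 TTR rule acts after randomisation, on a variable that the allocated product can affect and that is itself an outcome, and 4.6.2 does not place these patients. The interacting-drug rule also acts after randomisation when the drug is started during the trial; there 4.6.2 already limits the stated removal to INR and PT, and only follow-up is left open.

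If excluded patients leave, there are two outcomes. Leaving them out breaks intention to treat. Imputing them turns each into an adverse outcome: about 12% apparent at 10% exclusion and 22% at 20%, for an assumed true 2%. Exclusions partway through phases 2 to 4 can also add artificial discordant pairs. These sizes rest on assumed rates and on follow-up stopping, which the protocol does not state. The sample size is not affected. This is a cheap improvement worth making, not a fault in the primary calculation.

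**What to change.** Reconcile 4.3.2, 4.4, 4.6.1 and 4.6.2 as follows:

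- Keep 4.3.2 for conditions that can be checked before randomisation.
- State that every randomised patient stays under the twice-monthly bleeding and thromboembolism assessment of 4.5 until the end of phase 4, and stays in the intention-to-treat set with observed data. Impute only what is truly missing.
- State that the interacting-drug rule affects only the per-protocol INR and PT analysis, as 4.6.2 already says.
- Do not use phase 1 TTR to remove randomised patients from the main INR analysis without also reporting the INR result with them included. Otherwise the amendment would write selection on a product-affected variable into the primary analysis.
- For patients no longer taking study product, report events by randomised phase, with a sensitivity analysis limited to time on product. Attribution by randomised phase alone could pull product differences towards zero.

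None of this says who should continue or stop study product; it concerns follow-up and analysis only.

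The cost is a wording amendment and continued event assessment of a few patients for at most 3 × 28 = 84 days (12 weeks), within visits already planned.

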#### **4.5 Variables and outcomes**

Outcome data will be collected by the principal investigator ([name]). Laboratory tests (INR and TP) and clinical outcomes (thromboembolic events and bleeding) will be assessed twice a month; treatment adherence will be assessed monthly.

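### The phase 1 TTR rule excludes patients after randomisation, on the allocated product, by a measure derived from the primary outcome, and mislabels them as non-adherent

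*Protocol*

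**What the plan says.** Section 4.3.2 of the protocol lists among its exclusion criteria "patients not reaching a TTR of at least 70% in the first phase of the study (will be considered non-adherent to therapy").

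Section 4.4 gives the order of events. "Patients will be randomly allocated to one of the treatment sequences", and in phase 1 the patient "will start the randomly allocated treatment that will also be used in the second phase of the clinical trial". On duration: "The first phase of the study will last 21 days".

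Section 4.5 sets the measurement schedule: "Laboratory tests (INR and TP) and clinical outcomes (thromboembolic events and bleeding) will be assessed twice a month". Section 4.5.1 makes mean INR the primary outcome. Section 4.5.2 lists TTR as a secondary outcome, defined as the share of time with INR between 2.0 and 3.0, and calculates adherence from returned tablets. Section 4.4.2 also gives adherence as a purpose of the tablet count.

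Section 4.6.1 requires 48 patients and adds: "We plan to recruit 60 individuals (10 in each group) to compensate for possible dropouts or exclusions of patients". Section 4.6.2 plans a per-protocol paired t-test for INR and PT, and names only interacting drugs as the reason for leaving data out. The dichotomous outcomes, in which it includes TTR, are analysed by intention to treat with missing data counted as unfavourable.

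**The concern.** The rule stands among the entry criteria but can only be applied about three weeks after randomisation, when the patient has been taking a study product. The trial asks whether changing warfarin product disturbs anticoagulation. A patient whose INR leaves 2.0 to 3.0 on the first allocated product is part of the evidence on that question, and the rule removes that patient.

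Four things are at stake:

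- the estimated INR difference could be pulled towards equivalence, the conclusion the trial hopes to reach;
- exclusion rates could differ according to which product came first;
- poorly controlled patients would leave the TTR, bleeding and thromboembolism comparisons;
- the reserve between 60 and 48 could be used up.

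The non-adherence label is also wrong on the protocol's own terms, since a patient who takes every tablet can still fail the TTR threshold.

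**Working it through.** **1. The protocol's own sample size.** Inputs from section 4.6.1: difference 0.49, SD 0.29, alpha 5% (two-sided, section 3), power 90%. The two-independent-means formula gives

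n per group = 2 × [0.29 × (1.960 + 1.282) / 0.49]² = 7.36, rounded up to 8, and 8 × 6 = 48.

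The recruitment figure is 48 / (1 − 0.20) = 60. Both figures reproduce. The reserve is 12 patients (20%) for every cause of loss together, and the 13th loss takes the trial below 48.

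**2. Chance of falling below 48.** The protocol gives no TTR failure rate, so the rate is an assumption. P(13 or more lost of 60), exact binomial, with this rule as the only cause of loss:

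| Assumed failure rate | Expected left | P(fewer than 48) |
|---|---|---|
| 10% | 54 | 0.006 |
| 15% | 51 | 0.11 |
| 20% | 48 | 0.42 |
| 25% | 45 | 0.77 |
| 30% | 42 | 0.94 |
| 40% | 36 | 0.999 |

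With a further 10% lost for other reasons (assumed), the first three probabilities become 0.35, 0.68 and 0.89.

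**3. How many might fail.** Simulation with no product effect: patient means normal around 2.45, INR on days 0, 14 and 21, linear interpolation. The visit-to-visit SD is not in the protocol and is assumed.

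- If 0.29 is the SD of true patient means, visit SDs of 0.3, 0.4, 0.5 and 0.6 give about 24%, 33%, 43% and 53% failing. A visit SD of 0.2 gives about 17%.
- If 0.29 is the SD of observed means, so that it already contains visit noise (two readings each, assumed), visit SDs of 0.1 to 0.35 give about 11% to 16%.

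The plausible range is thus about 11% to 53%. Weekly readings instead of twice-monthly ones, with visit SDs of 0.3 to 0.6 and the first reading of 0.29, give about 26% to 57%, so the result does not hinge on the schedule.

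**4. Effect on the estimated difference.** One product is assumed to shift INR. A third of patients start on it (two of six sequences). Day 0 reflects the earlier product; days 14 and 21 reflect the allocated one.

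- *Uniform shift of 0.49:* the difference is 0.49 before and after exclusion. Patients are removed, but each remaining within-patient difference still contains the full shift.
- *Shift averaging 0.49, varying between patients with SD 0.4, visit SD 0.3:* about 51% of those who start on that product are excluded, against 24% of the others. The mean shift among retained starters falls to about 0.32. Over all retained patients it is (0.49 × 0.32 + 2 × 0.76 × 0.49) / (0.49 + 2 × 0.76) = 0.902 / 2.01 = 0.45. In that sum, the first 0.49 and the 0.76 are the retained shares. The shrinkage is 0.04 / 0.49 = 8%.
- *Across assumed mean shifts of 0.3 to 0.49, patient SD 0.2 to 0.4 and visit SD 0.3 to 0.5:* 2% to 8% shrinkage overall, and 7% to 34% among those who started on the shifted product.

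**5. Power if numbers fall.** For the planned paired t-test with SD 0.29 per period and zero correlation, the SD of a difference is 0.29 × √2 = 0.41. With 30 patients the noncentrality is 0.49 × √30 / 0.41 = 6.5, and power exceeds 0.99. The figure of 48 comes from an independent-groups formula applied to each sequence, so a paired analysis has power to spare.

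**6. Section 4.6.2 does not settle how these patients are counted.** For INR and PT it names only interacting drugs, so section 4.3.2 removes patients for a reason the analysis section does not mention. For the dichotomous outcomes, a patient removed after phase 1 has no data in phases 2 to 4 and would be unfavourable on every product. Such pairs are concordant and contribute nothing to McNemar's test.

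**The case against.** The case for leaving the rule alone has several sound parts.

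- **Bias.** A reader might infer that the rule necessarily biases the trial towards equivalence. The documents do not support that. The comparison is within patients, a uniform shift survives the exclusion intact, and unequal exclusion by first product does not by itself bias a paired difference. Shrinkage needs a product effect that varies between patients, and even then it is modest overall.
- **Sample size.** A reader might infer that this rule alone will probably use up the reserve and leave the trial underpowered. No visit-to-visit SD or failure rate is given. On some readings of the 0.29, failures stay near 11% to 16% and P(fewer than 48) is about 0.01 to 0.15. Power is hardly affected in any case.
- **Washout.** Section 4.4 presents phase 1 as time for the earlier formulation to clear, so its INRs are only partly an effect of the allocated product.
- **Intention to treat.** Section 4.6.2 already applies it to TTR and events, with a sensitivity analysis.
- **Real non-adherence.** Some excluded patients will truly be non-adherent or unstable.

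The first two points limit the size of the problem and stand. The third weakens the selection without removing it, because the allocated product is taken throughout phase 1. The fourth does not repair the rule, for the reason in step 6 of the working. The fifth is a reason to measure adherence by tablet count, as the protocol already plans. None of them changes the timing or basis of the exclusion.

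**Conclusion.** The rule is wrong as written and should be fixed. From the text alone, it excludes after randomisation, on the allocated product, by a measure derived from the primary outcome. It also gives those exclusions a label that conflicts with the protocol's own adherence measure.

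The likely damage to the primary estimate is small and conditional. It is about 2% to 8% shrinkage towards zero if the product effect varies between patients (SD 0.2 to 0.4, assumed), and none if the shift is uniform. That could mask a difference just above 0.49 but not a much larger one. The loss of poorly controlled patients from the TTR and event comparisons does not depend on that condition.

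The number remaining could fall below 48, since the reserve covers only 20% from all causes. Whether it would is not known from the protocol, and the shortfall would breach the stated minimum more than it would harm power.

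**What to change.** - Delete the phase 1 TTR criterion as a reason for exclusion after randomisation.
- If a stability screen is wanted, apply it before randomisation, from existing INR records. All participants already use warfarin at entry (section 4.3.1).
- Follow every randomised patient through all phases, and drop none from the INR, PT, TTR, bleeding or thromboembolism analyses because of phase 1 TTR.
- Use phase 1 TTR of at least 70% only to define a sensitivity analysis.
- Judge adherence by tablet counts.
- Reconcile section 4.3.2 with section 4.6.2, so that the reasons for leaving a patient out of an analysis are the same in both places.

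This is a small amendment. The cost is somewhat more variable INRs in the analysed set, which the surplus power of the paired design absorbs. It also frees the reserve of 12 for ordinary dropouts and interacting-drug exclusions.
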